### Power calculation

The sample size calculation for the core study is based on the test of the null hypothesis that the percentages of women with GWG within IOM guidelines in the two populations (intervention and control) are equal. To account for the uncertainty in these prior estimates, we calculated the sample size for different values of the percentage of women with weight within IOM guidelines in the control group in the range of 50–65%, with a risk difference of 15%, 20%, 25%, and 30%. While initially we targeted a total sample size of 350, the constraints of our funding timelines (which include a one-year CHIR grant extension) and a recruitment rate that was less than projected despite our best efforts, we revised our desired sample size to 242. Based on our a priori calculation, a sample size 111 per group corresponds to an absolute difference of 30% with our Nutrition + Exercise intervention, resulting in 30% of women in the treatment group having a GWG exceeding the IOM recommendations compared to 65% in the control group. With the revised sample size (i.e. assuming a 1:1 allocation ratio), the study will have power of 80% to yield a statistically significant result assuming a binomial distribution (using an intention-to-treat principle for the analysis) of the difference between percentages of women with GWG within IOM guidelines at alpha = 0.05. We hope to increase the sample size to 242 total participants in order to allow us to account for the two stratification variables – site (2 degrees of freedom) and baseline BMI strata (3 degrees of freedom).

The calculated sample size for the secondary outcome of maternal bone biomarker status is a total of 177 participants (allocation 1:1, α = 0.05, β = 20 for two-group t-test), based on literature with similar outcomes [55, 56]. A sample size was also calculated for the secondary outcome of infant whole body minus the head BMD. The total is 240 participants (allocation 1:1, α = 0.05, β = 20 for two-group t-test) based on the literature with similar primary outcomes in infant populations [57, 58]. For both sample sizes, a 15% attrition rate was calculated as a precaution in this type of clinical trial with follow-up.

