## Outcome measurements

Primary and secondary outcomes are summarized in Table 2 and described below.Primary outcome○ GWGSecondary outcomes○ Maternal and cord blood circulating bone markers: PINP, CTX-I, IGF-1, 25(OH)D, 1,25dihydroxyvitamin D○ Maternal bone status at six months postpartum: whole-body bone mineral content (BMC), whole body BMD, lumbar spine BMD○ Infant bone status at six months of age: whole body minus the head BMCOther outcomes○ Maternal body weight and fat mass○ Maternal metabolic status (including fasting glucose and lipid profiles, leptin and adiponectin)○ Maternal blood pressure○ Maternal pregnancy outcomes such as gestational diabetes and pre-eclampsia○ Infant birth outcomes such as birth weight and body fat mass at six months○ Safety outcomes○ Quality of life using the EQ-5D questionnaire○ Healthcare costs○ Maternal and cord blood gene variant profiles

**Table 2 Tab2:** Analysis plan: objectives, outcomes, hypotheses, and methods of analysis

Objective	Hypothesis	Outcome measure (type of outcome: B = binary or C = continuous)	Methods of analysis
1. Primary	An experimental combined Nutrition + Exercise intervention will increase the percentage of pregnant women who achieve GWG within current recommendations when compared with standard care provided in the primary care community setting	Proportion of women who are within the BMI appropriate GWG according to the IOM guideline for GWGs (B)	Logistic regression
2. Secondary	An experimental combined Nutrition + Exercise intervention will lead to better maternal and child bone health outcomes when compared to standard care	*• Maternal and cord blood circulating bone markers (C)* ○ Bone biomarkers: PINP, CTX-I, IGF-1, 25(OH)D, 1,25(OH)_2_D *• Maternal bone status at 6 months postpartum (C)* ○ Whole body bone mineral content, whole body BMD, lumbar spine bone mineral density by DXA scan *• Maternal fat mass (C)* *• Maternal blood glucose, lipid profile, leptin, and adiponectin* *• Maternal blood pressure (C)* ○ Diastolic BP ○ Systolic BP *• Maternal pregnancy outcomes (B)* ○ Gestational diabetes ○ Pre-eclampsia *• Infant bone status at 6 months of age (C)* ○ Whole body minus the head bone mineral content by DXA scan *• Infant outcomes* ○ Birth weight z-score(C) ○ Body fat mass (B)	Regression analysis *We will use logistic regression for binary outcomes and linear regression for continuous outcomes

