The primary outcome of GWG was selected because it is the key clinical problem we are addressing with our Nutrition + Exercise intervention. Pre-pregnancy obesity and excess GWG are the strongest maternal characteristics associated with offspring obesity [9, 11, 59] and childhood metabolic dysfunction [60]. Excess GWG in pregnancy is a major clinical challenge affecting Canadian women who enter pregnancy overweight and even women of normal pre-pregnancy weight [61, 62]. At the national level, a cross-sectional study on pregnancy experiences in Canada determined that over one-third of women entered pregnancy overweight or obese and nearly 60% experienced GWG greater than that recommended by the IOM recommendations for GWG [63]. The Alberta Pregnancy Outcomes and Nutrition prospective cohort study reported similar statistics with a greater number of overweight and obese women (80%) gaining excess weight during pregnancy [64]. Likewise, in the Hamilton region, data from the Family Atherosclerosis Monitoring In earLY life birth cohort demonstrated that > 50% of women entered pregnancy with a pre-pregnancy BMI of > 25.0 kg/m^2^ and > 50% exceeded the IOM guidelines for GWG [65]. Evidence to date suggest that the most convincing approach to achieve appropriate GWG is an intervention combining physical activity and nutrition, in combination with weight monitoring [1, 20, 21].

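### The power calculation states its hypothesis and 80% power for women within the IOM range but takes its event rates from women exceeding it, so the 80% is not established for the primary outcome

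*Protocol article*

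**What the plan says.** Table 2 (Outcome measurements) gives the primary outcome as "Proportion of women who are within the BMI appropriate GWG according to the IOM guideline for GWGs (B", where B marks a binary outcome. The Power calculation section follows this at first. It tests the "null hypothesis that the percentages of women with GWG within IOM guidelines in the two populations (intervention and control) are equal", and it varies "the percentage of women with weight within IOM guidelines in the control group in the range of 50–65" (per cent) "with a risk difference of 15%, 20%, 25%, and 30" (per cent). Its closing power statement, 80% at alpha 0.05, is again about percentages within the guideline.

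Between these statements the outcome changes. The section says that "a sample size 111 per group corresponds to an absolute difference of 30% with our Nutrition + Exercise intervention", and continues: "resulting in 30% of women in the treatment group having a GWG exceeding the IOM recommendations compared to 65% in the control group". These are the only event rates attached to 111 per group.

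The Discussion gives background rates, all for exceeding. Nationally, "nearly 60% experienced GWG greater than that recommended by the IOM recommendations for GWG". A regional cohort is reported at more than 50%, and overweight and obese women in a third study at 80%. The article gives no share of women below the range in either arm.

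**The concern.** A woman can be below, within or above the range. The primary outcome counts both below and above as failure. A rate of exceeding therefore fixes the rate of being within only if the below-range share is also known. The section supplies one and claims power for the other.

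At stake is whether the quoted 80% applies to the hypothesis the trial will test. The Discussion relies on the predetermined sample size to say the stated hypothesis can be properly tested, and the target was cut from 350 to 242 in this same paragraph. A reader who wants to know what difference in the primary outcome the trial can detect cannot find it here.

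**Working it through.** **Inputs.** Two-sided alpha 0.05 (Statistical methods); 1:1 allocation, 80% power, 111 per group, 65% and 30% exceeding (Power calculation); 87% retention to the 36–38 week visit (Discussion). The below-range share is not in the document. I vary it from 0 to 20% in control, as an assumption.

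**Formulas.** With d = |p1 − p2| and p̄ the mean of the two rates:

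- n = [1.960·√(2p̄(1−p̄)) + 0.842·√(p1(1−p1) + p2(1−p2))]² / d²
- with continuity correction, n_c = (n/4)·[1 + √(1 + 4/(n·d))]²
- power at N per group = Φ{[d·√N − 1.960·√(2p̄(1−p̄))] / √(p1(1−p1) + p2(1−p2))}; the corrected version replaces d by d − 1/N.

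**Step 1: do the labels agree?** 100 − 65 = 35, so at most 35% of controls are within. The stated range for controls within starts at 50%. The national figure of nearly 60% exceeding leaves at most about 40% within, and the regional figure leaves under 50%. As a rate of exceeding, 50–65% fits these data well.

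**Step 2: does 111 reproduce?** 65 − 30 = 35 points, not 30. For 65% against 30%, p̄ = 0.475 and n = (1.384 + 0.557)²/0.1225 = 30.8.

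| Rates | n per group | Corrected | Power at 111 |
|---|---|---|---|
| 65% v 30% | 31 | 37 | 99.98% |
| 65% v 35% (a 30-point gap) | 43 | 49 | 99.6% |
| 65% v 95% (65% read as within, plus 30 points) | 27 | 34 | – |
| 65% v 45.5% (a 30% *relative* fall) | 101 | 111 | 83.7% |
| 65% v 45% | 96 | 106 | 85.5% |

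No 30-point difference in the 50–65% grid needs more than 49 per group at 80% power. A 30% relative fall with continuity correction gives 111. So does 65% v 45% inflated for retention: 96/0.87 = 110.3, rounded up to 111. The origin of 111 therefore cannot be settled from the article.

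**Step 3: translate to the primary outcome.** Within = 100 − exceeding − below. The difference in within is therefore the fall in exceeding minus any rise in below.

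At the printed rates the fall is 35 points. With equal below shares of 0–20%, within goes from 35–15% to 70–50%, and power at 111 exceeds 99.9%. The uncorrected detectable difference at 80% power, and the rise in below that would use up the margin, are:

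| Below, control | Within, control | Detectable difference | Rise needed (35 − difference) |
|---|---|---|---|
| 0% | 35% | 18.6 | 16.4 |
| 5% | 30% | 18.3 | 16.7 |
| 10% | 25% | 17.8 | 17.2 |
| 15% | 20% | 16.9 | 18.1 |
| 20% | 15% | 15.8 | 19.2 |

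**Step 4: sensitivity to a smaller planning effect (assumed, 65% to 45.5%).** The fall is now 19.5 points. Power for within at 111 per group, over below shares of 0–20% in control:

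| Rise in below under intervention | Uncorrected | Corrected |
|---|---|---|
| 0 points | 84–93% | 80–90% |
| 5 points | 59–74% | 54–69% |
| 10 points | 30–43% | 26–36% |

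For example, with 10% below in control and 15% under intervention, within is 25% v 39.5% and power is 64% (58% corrected).

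**The case against.** The strongest reply is that the section names the right outcome three times, in the null hypothesis, the control range and the power statement, so one sentence about exceeding is a slip that costs nothing. In support, at the printed rates power for the primary outcome is far above 80%. Even with inadequate gain at 10% in control and 20% under intervention, within is 25% v 50% and power is 97.5% (96.5% corrected). No source in the article suggests that inadequate gain would rise, and the design works against it: plans are set to each woman's energy requirement and revised if monitoring shows weight loss or excess gain (Interventions).

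Much of this stands, and it rules out some stronger readings. A reader might infer that the trial is underpowered, or that it could reduce excess gain as planned and still fail. The documents do not support that. The only effect they print is 65% to 30%, the smaller effect in Step 4 is back-solved and not unique, and the rise in inadequate gain is assumed. A reader might also infer that 50–65% cannot possibly be a within rate. That too goes too far: the background rates are for other populations, while this trial expects mostly university-educated women and gives controls nutritionist counselling. Nor is the lack of a planned three-category analysis a fault, since an analysis plan not shown may contain it.

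What does not stand is the idea of a harmless slip. Changing the word in that sentence does not rescue it: 65% within in control against 30% under intervention would be a harm, and 65% rising to 95% needs only 27–34 per group. No relabelling of the printed rates yields 111 at 80% power.

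**Conclusion.** The point holds as an internal contradiction in the power calculation. The printed rates are for exceeding, the claimed power is for within, and the missing below-range share means one cannot be converted into the other. The 80% is not established for the primary outcome. Separately, the printed figures disagree with each other (30 against 35 points) and with the sample size (31–37 or 43–49 per group, against 111).

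The direction of the error is unknown. Taken literally, the rates imply more than 99% power for exceeding and ample power for within, unless inadequate gain rises by roughly 16–19 points. If the real planning effect was nearer 20 points, the margin is thin and a 5-point rise would bring power to somewhere between the mid-50s and the mid-70s per cent. Which case applies depends on planning assumptions the article does not state. All figures here are unadjusted two-proportion calculations.

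**What to change.** Rewrite the Power calculation paragraph on the primary outcome:

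1. State the assumed below, within and above percentages for each arm. The control within rate should agree with the Discussion's background data, at most about 35–40%, or a higher figure should be justified.
2. Reconcile the 30-point difference with the 65% and 30% rates, say whether 30% was absolute or relative, and show how 111 was obtained, including any continuity correction or allowance for attrition.
3. Restate power for within over a plausible range of below-range shares, or give the detectable difference: at 111 per group and 80% power, about 18–19 points from a control within rate of 25–35%.

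This costs one paragraph. The endpoint, sample size and data collection are unchanged. As an optional addition, reporting below, within and above by arm beside the primary result would show whether fewer women exceeding was offset by more women below. It uses data already collected.

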## Methods/design

### Trial design

The BHIP study is a two-arm, two-site prospective RCT. This study is designed as a prospective superiority trial, with 1:1 allocation ratio to either the Intervention group (i.e. Nutrition + Exercise intervention: high-dairy nutrition intervention combined with structured exercise) or the Control group (i.e. usual care as per National Health Canada recommendations) during pregnancy. The study is open-label with blinded endpoints. The study protocol is described following the standard protocol items: recommendations for interventional trials (SPIRIT) guidelines [34]. See Additional file 1 for the SPIRIT checklist and Additional file 2 for the WHO trial registration data set.

The core BHIP trial follows women up to delivery as the primary outcome relates to GWG. The Bone-BHIP study is an extension of the core BHIP trial that continues a follow-up of the women and their offspring until six months after delivery, with the objective to assess maternal and infant bone status. This trial is registered at ClinicalTrial.gov (NCT01689961). The BHIP trial is conducted by collaborative research teams at McMaster University (Hamilton, ON) and Western University (London, ON) in Canada. The study takes place in academic hospitals and community healthcare clinics in London, Burlington, and Hamilton, Ontario, Canada. Recruitment is facilitated by healthcare professionals (e.g. family doctors and midwives) who ask their patients for consent to be contacted by the BHIP study team, as well as poster advertisements in midwifery, family practice, and ultrasound clinics, at community sites such as the YMCA, libraries, and coffee shops, and on Facebook or Kijiji.

Study recruitment began in January 2013 and is expected to be completed by April 2018, reaching the a priori calculated sample size of 242 participants for our primary outcome. All participants who sign consent to contact forms receive a phone call by study personnel and are provided a general overview of the study and expectations using a scripted text. Figure 1 outlines the participant’s timeline in the BHIP study. Participants are screened for eligibility during the telephone interview according to the criteria list below. Eligible women are enrolled in the study and sign informed consent by the end of the first trimester of pregnancy (i.e. 12–17 weeks of gestation).

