### Statistical methods

The analysis and reporting of the results will follow the SPIRIT statement for reporting RCTs [53]. The process of patient selection and flow throughout the study will be summarized using a flow-diagram (Fig. 2).

The results of patient baseline characteristics and outcome variables (both primary and secondary) will be summarized using descriptive summary measures: expressed as mean (standard deviation) or median (range) for continuous variables and n (%) for categorical variables. All statistical tests will be performed using two-sided tests at the 0.05 level of significance. Binary outcomes will be analyzed using logistic regression and continuous outcomes will be analyzed using linear regression. All analyses will account for stratification by including study site and participants’ BMI category in the models. For all models, the results will be expressed as estimate of the difference for continuous outcomes (odds ratio [OR] or relative risk [RR] for binary outcomes), corresponding two-sided 95% confidence intervals (CI) and associated *p* values. *P* values will be reported to three decimal places with values < 0.001 reported as < 0.001. The Hosmer–Lemshow will be used to assess goodness-of-fit for logistic regression and explore the residuals to assess goodness-of-fit and model assumptions for linear regression.

An intention-to-treat principle will be adopted to analyze all outcomes. Multiple-imputation will also be used to handle missing data during data collection. Sensitivity analyses will be performed using some of the commonly used RCT patient-level methods (e.g. generalized estimating equations, the random-effect model which account for the potential correlation within sites, etc.) to assess the robustness of the results [54]. All the analyses will be done using SAS 9.2 (Cary, NC, USA) or SPSS 13 (Chicago, IL, USA). Table 2 provides a summary of the planned methods of analyses for each outcome and subgroup.

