For the timely recruitment of study participants, challenges included prolonged ethics approval processes at secondary recruitment sites, reduced recruitment at community family practices due to influx of immigrants who were non-English speaking (thus not eligible), and competition with other studies sampling pregnant women. In light of these, we have taken measures to achieve the predetermined sample size based on a power analysis for the primary outcome so that the integrity of the study is preserved and the results are able to properly test the stated hypothesis and provide the needed new knowledge. To expand recruitment at McMaster University a new local study site was set up in a nearby city, Burlington, Ontario, with the collaboration of midwifery and obstetric clinics, as well as the local hospital. This partnership is very successful thus helping to achieve the recruitment goal. To date, retention after randomization to the study visit at 36–38 week of gestation when we assessed our primary outcome is 87%. To maximize retention of participants, we implemented a number of procedures such as study visit times at the convenience of the participants, including home visits. We also offered in-person, over the phone, and email correspondence to keep participants engaged. For participants in the intervention group, providing them with the dairy products (which are an integral part of the intervention) increases the likelihood of consuming the recommended amount. For the exercise component, participants receive a free pedometer as a self-motivation tool to reach their step count goals. Lastly, for both groups, participants are compensated on three occasions with $25 gift cards that they can redeem at a local grocery store.

If effective, this RCT will generate high-quality evidence to refine the nutrition guidelines during pregnancy to improve health of women during pregnancy and their offspring in early life, including acquisition of a strong skeleton.

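### The primary power statement is internally inconsistent and cannot be reproduced: 111 per group gives 80% power for a difference of about 19 points, not 30 or 35.

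*Protocol article*

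**What the plan says.** The Power calculation section of the protocol article tests whether the percentages of women gaining within the IOM guidelines are equal in the two arms. It says that control rates within guidelines of 50–65% and risk differences of 15, 20, 25 and 30% were explored. It then states: "a sample size 111 per group corresponds to an absolute difference of 30% with our Nutrition + Exercise intervention, resulting in 30% of women". That last figure belongs to the intervention arm, and the sentence ends by naming the event and the comparator: "having a GWG exceeding the IOM recommendations compared to 65% in the control group". Allocation is 1:1, and "the study will have power of 80% to yield a statistically significant result assuming a binomial distribution" for a test "of the difference between percentages of women with GWG within IOM guidelines at alpha = 0.05". Statistical methods adds: "All statistical tests will be performed using two-sided tests at the 0.05 level of significance".

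The step from 222 (2 × 111) to 242 is explained by the two stratification variables, with site given 2 degrees of freedom and BMI 3. A 15% attrition rate is mentioned only after the two secondary-outcome sample sizes, and for those two. The Discussion reports that "retention after randomization to the study visit at 36–38 week of gestation when we assessed our primary outcome is 87" per cent.

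On the origin of 242, Power calculation says "While initially we targeted a total sample size of 350" and gives funding timelines and slow recruitment as the reasons for the cut. Trial design speaks of "reaching the a priori calculated sample size of 242 participants for our primary outcome", and the Discussion calls the sample size predetermined.

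**The concern.** The sentence gives two different effect sizes, and a sample of 111 per group is far larger than either requires at 80% power. It also switches outcome. The hypothesis and the 50–65% range refer to women within guidelines, while the 30% and 65% refer to women above them. Because some women gain too little, one is not 100% minus the other.

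Readers use this statement to interpret the result. Told that the trial was sized for 30 to 35 points, they would misread a null result or a difference of 15 to 20 points. They also cannot tell what power remains after the loss that the article itself reports.

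**Working it through.** **Inputs.** Two-sided alpha 0.05 (Statistical methods); 80% power, 1:1 allocation, 111 per group, 65% and 30% exceeding (Power calculation); 87% retention to the primary-outcome visit (Discussion).

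**Formula per group**, with d = |p1 − p2| and p̄ their mean:

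n = [1.960·√(2p̄(1−p̄)) + 0.8416·√(p1(1−p1) + p2(1−p2))]² / d²

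Continuity-corrected: n_c = (n/4)·[1 + √(1 + 4/(n·d))]²

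**Step 1. The stated effects.** 65% − 30% = 35 points, not 30.

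- 65% vs 35%: (1.960·0.7071 + 0.8416·0.6745)² / 0.30² = 3.817/0.09 = 42.4, so 43; corrected 48.8, so 49.
- 65% vs 30%: (1.960·0.7062 + 0.8416·0.6614)² / 0.35² = 3.767/0.1225 = 30.8, so 31; corrected 36.2, so 37.

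Uncorrected power at 111 per group is 99.6% and 99.98%. A 15% loss allowance raises these sizes to at most 58 and 44. Unpooled variance, the arcsine method, one-sided testing and higher power do not bring either effect to 111. Using the listed within-guideline control rates does not help: a 30-point rise needs 39 (45 corrected) from 50% and 27 (34) from 65%.

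**Step 2. What 111 does detect at 80% power.**

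| Starting rate and direction | Uncorrected | Corrected |
|---|---|---|
| 65% downward, or 35% upward | 18.6 points | 19.5 points |
| 50% upward | 18.4 points | 19.2 points |
| 65% upward | 16.6 points | 17.4 points |

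**Step 3. Where 111 might come from.** Two back-solutions fit:

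- 65% to 45.5%, a 30% relative reduction (0.65 × 0.70 = 0.455; 19.5 points): (1.378 + 0.580)² / 0.195² = 100.9 uncorrected; corrected 110.9, so 111.
- 65% vs 45% (20 points, a listed difference): 95.9, so 96 uncorrected. Then 96 × 1.15 = 110.4, or 96/0.87 = 110.3; both round up to 111. (96/0.85 would give 113.)

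**Step 4. Within versus exceeding.** If 65% of controls exceed the guidelines, at most 100 − 65 = 35% can be within them. That lies outside the 50–65% within-guideline range explored in the same section.

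**Step 5. Loss.** 242 × 0.87 = 210.5, about 105 per group. Power = Φ{[(d − c)·√n − 1.960·√(2p̄(1−p̄))] / √(p1(1−p1) + p2(1−p2))}, with c = 0 or 1/n. For 65% vs 45.5% at n = 105:

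- Uncorrected: (0.195·10.247 − 1.378)/0.6895 = 0.899, power 81.6%.
- Corrected: (0.1855·10.247 − 1.378)/0.6895 = 0.757, power 77.6%.

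If 111 per group must be evaluable, 111/0.87 = 127.6, so 128 per group or 256 in total.

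**Step 6. Degrees of freedom.** Two sites use 2 − 1 = 1. Four BMI categories use 3, as stated.

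**The case against.** The contradiction in the stated effect and its mismatch with 111 cannot be argued away. The case on the other side concerns how much more may be concluded, and most of it stands.

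- **A relative reduction written as absolute.** The exact match at 65% to 45.5% invites this reading. But the article mentions neither a relative reduction nor a continuity correction, and its grid is in absolute differences. It includes 20 points but not 19.5, and 65% vs 45% with a loss allowance gives 111 equally well. The document cannot separate the two, so neither should be written in as the design assumption.
- **The primary calculation ignores loss.** The article never says that 111 means evaluable women, and under the second back-solution loss is already included. What can be said is that no allowance is stated for the primary outcome. In practice the 20 extra women would absorb about 8% loss (20/242), though the article gives stratification as their purpose.
- **The trial falls below 80% power.** This depends on the continuity correction. The planned logistic regression uses none, and the uncorrected figure at 105 per group is 81.6%. Planned multiple imputation deals with missing values but is not a sample-size allowance.
- **The cut from 350 was hidden.** It was not: Power calculation discloses it with reasons. The wording elsewhere is a minor inconsistency.

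**Conclusion.** The primary power statement is wrong as written. Its rates differ by 35 points where it says 30, and 111 per group has over 99% power for either difference. At 80% power it detects about 18.5 to 19.5 points for the 65% starting rate taken downward, so the stated effect is too large by roughly 10 to 16 points. This rests on a two-sided 0.05 test, 1:1 allocation and the standard two-proportion formula. The continuity correction moves the result by about one point, and a within-guideline control rate of 65% would lower it to about 17. The rates also belong to a different outcome from the one tested.

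The loss issue is smaller: power for 19.5 points at about 105 per group is 77.6% or 81.6%, depending on the correction. A reader might infer that the trial is underpowered, or that the origin of 111 is known. The document supports neither.

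**What to change.** Retrieve the original calculation and rewrite the sentence in Power calculation so that it gives:

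1. the assumed control and intervention percentages of women within guidelines;
2. the method, including whether a continuity correction was used;
3. any loss allowance for the primary outcome, or a statement that there was none;
4. that 111 per group gives 80% power for a difference of roughly 19 points, not 30 to 35, with the exact figure tied to the rates in item 1;
5. the power at about 105 evaluable women per group (about 78–82% for 19.5 points, depending on the continuity correction).

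Correct site to 1 degree of freedom. In Trial design and the Discussion, describe 242 as the target revised from 350. Do not assign the 20 extra women a new purpose unless the records support it.

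The cost is retrieving the inputs and editing a few sentences. Enrolment, conduct and analysis do not change.
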